### **Effectiveness assessments**

There will be two examinations for both groups, at baseline and 24 months (after 2 years intervention). Indicators including BP, BMI and lifestyle factors will be assessed.

All outcome assessments will be conducted at baseline and at 24-month follow-up in exactly the same way in the clinics for all patients, irrespective of their assignment to intervention or control group. For the intervention patients, monthly follow-up visits will be made within the 2 years duration to document the BP and lifestyle factors.

177

178 **Statistical Methods:**

179 All patients who attended follow-up visits at 24 months and had complete data for the  
180 primary outcome and other variables were included in the analysis. The baseline  
181 differences between patients included and unincluded, patients in the intervention  
182 group and those in the control group, will be examined by mixed-effects model. All  
183 patients who attend follow-up visits at 24 months and have complete data for the  
184 primary outcome may be included in the analysis, without imputation for missing data.  
185 The intervention effect will be performed as the difference between two groups, it will  
186 be calculated as intervention (values at 24 months minus values at baseline) minus  
187 control (values at 24 months minus values at baseline), and evaluated by  
188 mixed-effects models (PROC MIXED for continuous variables, PROC GLIMMIX for  
189 categorical variables), which included a random cluster effect (workplace). Group  
190 (intervention, control), all the baseline covariates, and potential interaction terms were  
191 used for adjustment in all models. The subgroup analyses of primary outcome will be  
192 conducted to assess the intervention effect on subgroups of education, occupation  
193 status, workplace ownership, and workplace-affiliated hospital. To evaluate the  
194 robustness of the results of the primary analyses, multiple-imputation method was  
195 adopted to handle missing data on outcome and covariates in a sensitivity analysis.  
196 The results will be summarized as rate (%), mean, standard deviation (SD), standard  
197 error (SE), and 95% confidence interval (CI) when appropriate. All data analyses will  
198 be conducted using SAS 9.4 (SAS institute, Cary, NC, USA) and a two-sided *P*-value

<0.05 will be considered statistically significant.

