### **Sample Size Considerations:**

The study is designed as an effectiveness trial of active interventions, compared with the usual care group. On the basis of previous literature, we expected that 20% of patients in the control group would be properly controlled, whereas we expected patients in the intervention group to increase this to 50% control at 24-month follow-up. Considering the intervention benefits and ethical issues, the study was designed to recruit patients using a 3:1 ratio. Cluster randomization power analysis was performed for the two independent proportions, and with a 2.5% type I error and intra-cluster correlation coefficient (ICC) of 0.01, we estimated that a sample size of 3,000 intervention patients (cluster size 75) and 1,000 control patients (cluster size 50) would provide 90% power to detect an improvement of 25% in BP control between the two groups and allowing 20% loss to follow-up in each group. To ensure an enough power, 3,600 intervention patients and 1,200 control patients were recruited in this study.

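### Two inclusion rules for the primary analysis conflict, and both limit it to patients seen at 24 months, which can bias the result in either direction

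*Protocol*

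**What the plan says.** All of this is in the protocol, under Statistical Methods (which follows Effectiveness assessments) and Sample Size Considerations.

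- First rule: patients attending at 24 months with complete data for the "primary outcome and other variables were included in the analysis".
- Second rule, two sentences later: attenders with a complete "primary outcome may be included in the analysis, without imputation for missing data".
- Adjustment, in all models: "intervention, control), all the baseline covariates, and potential interaction terms were" used.
- Imputation: to check the "robustness of the results of the primary analyses, multiple-imputation method was" "adopted to handle missing data on outcome and covariates in a sensitivity analysis".
- Selection check: patients included in the analysis are compared at baseline with those not included.
- Planned loss: the sample size is stated as "allowing 20% loss to follow-up in each group".

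Under Study design and Effectiveness assessments, both arms are examined at baseline and at 24 months. Only intervention patients have monthly visits in between. Under Clinic component, project officers supervise and assist that attendance.

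**The concern.** The primary analysis population is not uniquely fixed. The first rule needs a complete outcome and complete other variables, which are not listed. The second needs the outcome only, and its verb makes inclusion optional. A patient with a valid 24-month blood pressure but a missing blood test is out under the first and may be in under the second. The Appendix B questionnaire has four blood tests and nine disease or family-history items with an unclear option, so incomplete records are to be expected.

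Under either rule, the headline result describes only those who came back at 24 months. Regular clinic contact is part of the intervention and is scheduled in one arm only, so the arms may lose different numbers of patients, or lose them for different reasons. If return is related to blood pressure control in a way that the baseline covariates do not explain, the comparison of completers is no longer a comparison of the arms as assigned. At stake are the size of the primary effect and the freedom to choose a set after the data are seen.

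**Working it through.** **The two rules side by side.** The first rule gives attenders with complete outcome and complete other variables; the second gives attenders with complete outcome. The first set lies inside the second. They coincide in the adjusted model if every attender who lacks one of the other variables also lacks a model covariate, because a model fitted without imputation drops such records. The text does not say that this is meant, and the second rule would then not describe the patients actually analysed.

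**Numbers excluded.** Recruited: 3,600 + 1,200 = 4,800 (Sample Size Considerations).

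- Lost at 20%: 0.20 × 4,800 = 960 (720 intervention, 240 control).
- Kept under the second rule: 4,800 − 960 = 3,840.
- Kept under the first rule if 5%, 10% or 20% of these lack another variable (assumed; the protocol gives no figure): 3,840 × 0.95 = 3,648; × 0.90 = 3,456; × 0.80 = 3,072.

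**The plan's power figure.** The protocol states 90% power for 3,000 and 1,000 patients, ICC 0.01, a 25-point improvement and 20% loss. This does not reproduce. Design effects are 1 + 74 × 0.01 = 1.74 (intervention) and 1 + 49 × 0.01 = 1.49 (control). Effective numbers after loss are 2,400 / 1.74 = 1,379 and 800 / 1.49 = 537. For 45% against 20%, the standard error is √(0.45 × 0.55 / 1,379 + 0.20 × 0.80 / 537) = 0.022, so 25 points is more than 11 standard errors. Power is above 99.9% at 2.5% or 5%, one- or two-sided. The point here does not depend on the 90%: losing one patient in five does not threaten power.

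**Effect on the estimate.** I take the planning rates as the completer rates: 50% in the intervention arm, and for the control arm "we expected that 20% of patients in the control group would be properly controlled". The completer difference is 30 points. I assume the same baseline control rate in both arms, among completers and among all enrolled, so that the baseline terms of the change-from-baseline contrast cancel. For each arm, with lost fraction L and control rate r among the lost:

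rate in all enrolled = (1 − L) × completer rate + L × r

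Apart from the 20% loss, all values of L and r are assumptions.

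| L, interv. / control | r, interv. / control | Intervention | Control | Difference (points) |
|---|---|---|---|---|
| 20% / 20% | 20% / 20% | 0.40 + 0.04 = 0.44 | 0.16 + 0.04 = 0.20 | 24 |
| 20% / 20% | 35% / 20% | 0.40 + 0.07 = 0.47 | 0.20 | 27 |
| 20% / 20% | 50% / 20% | 0.40 + 0.10 = 0.50 | 0.20 | 30 |
| 20% / 20% | 35% / 5% | 0.47 | 0.16 + 0.01 = 0.17 | 30 |
| 10% / 30% | 35% / 10% | 0.45 + 0.035 = 0.485 | 0.14 + 0.03 = 0.17 | 31.5 |
| 20% / 20% | 0% / 100% | 0.40 | 0.16 + 0.20 = 0.36 | 4 |
| 20% / 20% | 100% / 0% | 0.40 + 0.20 = 0.60 | 0.16 | 44 |

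Completers show 30 points in every row. That figure may be too high, right or too low for all enrolled.

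**Counting every lost patient as uncontrolled.** At 20% loss in both arms: 0.40 − 0.16 = 24 points. At 10% and 30% loss: 0.9 × 0.50 − 0.7 × 0.20 = 0.45 − 0.14 = 31 points. The second result exceeds the completer difference, so this rule is not conservative when the control arm loses more.

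**The case against.** The strongest defence is that bias is possible but not shown. If loss depends only on the baseline covariates in the model, the completer estimate need not be biased. The plan already includes imputation of outcome and covariates and a baseline comparison of included and excluded patients, so a result that uses all patients will be produced. The dispute over it is then about which analysis is called primary. The 960 is a planning allowance, not a count, and the two sets may coincide in the adjusted model.

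Much of this stands and limits the point. A reader might infer that the completer analysis overstates the effect. The documents do not support this: they give no outcomes for lost patients, and the 24- and 27-point results come from assuming that the lost in the intervention arm do worse than its completers while the lost in the control arm match theirs. Better retention under monthly supervision could equally produce an understatement.

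A reader might also infer that patients who stop attending the programme are excluded. They are not, if they attend at 24 months. Nor do the documents say that control patients have no contact for two years. They say only that no study examination is scheduled; usual care continues, and the Study design criteria require every workplace, control workplaces included, to have a project officer and a designated clinic.

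The defence does not remove the conflict between the two rules. Comparing baseline characteristics describes selection without correcting it, and a sensitivity analysis does not settle which number is the trial's answer.

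**Conclusion.** The point holds in this form: the protocol states two inclusion rules that do not agree, both confine the primary analysis to 24-month attenders, and the resulting estimate can be biased in a direction that the documents do not determine. At the planned loss, 960 of 4,800 patients are left out; the first rule would remove more, by a number that cannot be known from the protocol. In the illustrations with moderate dropout rates, the difference for all enrolled lies between 24 and 31.5 points against 30 in completers. The bounds of 4 to 44 are arithmetic limits, not expectations. The contradiction and the restriction to attenders can be read directly from the text; the sizes rest on assumed outcomes and loss among the missing.

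**What to change.** Replace both inclusion sentences with one primary set: all enrolled patients, analysed by the arm to which their workplace was assigned.

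- Make the planned multiple imputation of outcome and covariates the primary analysis. Impute by arm, with workplace and baseline blood pressure in the imputation model, and use the monthly blood pressure readings as auxiliary data in the intervention arm.
- Keep the completer analysis as a sensitivity analysis, defined by a complete 24-month outcome only.
- Imputation assumes that data are missing at random. Add a sensitivity analysis that varies the control rate among lost patients separately in each arm. Counting all lost patients as uncontrolled may be one case, but should not be presented as necessarily conservative.
- Keep the baseline comparison of patients with and without 24-month data, as description.

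The cost is wording and a little analysis work, since the imputation is already planned. The reported effect or its precision may change slightly.

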**Study design**

*CONFIDENTIAL*

*Division of Prevention and Community Health, National Center for Cardiovascular Disease, China*

The study is a two-phase design. First, a cross-sectional survey designed to evaluate the prevalence and management of hypertension among Chinese working population. Then, a cluster-controlled trial conducted to test the effect of a multicomponent intervention strategy on improving hypertension control in workplaces.

For this program, a coordinating center will be established at Fuwai Hospital, Beijing. Then, 20 urban medical institutions will be selected as sub-centers, representing various geographic locations in China. Subsequently, 2 to 4 workplaces will be recruited by each sub-center, to test the feasibility of the protocol in work settings, all of which should meet the following criteria: (1) more than 50 patients can be recruited per site; (2) workplaces within the same sub-center should be matched by sector, ownership, size, economic level and medical condition; (3) none similar programs were conducted before; (4) non-medical institutions; (5) agrees to participate in the program for a minimum of 2 years; (6) agrees to arrange at least one full-time or part-time project officer to execute the workplace wellness program; and (7) can select a designated hospital clinic for implementing the standardized HTN management for 2 years.

Within each sub-center, 1 to 3 workplaces will be assigned to the intervention group, and one workplace assigned to the control group, with approval from manager of each workplace. To minimize the potential imbalance between groups, workplaces assigned to the intervention and control group within each sub-center, should be matched by sector, ownership, size, economic level and medical condition. Within each sub-center, at least 50 potential participants will be selected and invited for

89 baseline assessments at each workplace, and the patients will be allocated to  
90 intervention or usual care in a 3:1 ratio.

91 For the intervention patients alone, there will be monthly follow-up visits within  
92 the 2 years duration by their physicians. Patients in the control group carry on with  
93 their usual health care.

94

95 **Study Duration:**

96 Subjects will receive intervention for a minimum of 24 months.

97

98 **Study Inclusion and Exclusion Criteria:**

99 **Inclusion Criteria:**

- 100 1. Subject has a clinical diagnosis of HTN;
- 101 2. Subject is aged 18 to 60 years;

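### Workplaces are matched and assigned within sub-center, but the stated outcome models name only workplace; sub-center should be added, though the likely effect on the result is small

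*Protocol*

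**What the plan says.** Protocol, Study design, makes sub-center the unit within which the comparison is built. It states that "20 urban medical institutions will be selected as sub-centers, representing various geographic locations in China" and that "2 to 4 workplaces will be recruited by each sub-center". A recruitment criterion is that "workplaces within the same sub-center should be matched by sector, ownership, size, economic level and medical condition". Assignment follows the same structure: "Within each sub-center, 1 to 3 workplaces will be assigned to the intervention group, and one workplace assigned to the control group", and this is done "with approval from manager of each workplace". No random step is described there, although Sample Size Considerations refers to a cluster-randomization power analysis. The next part of Study design sets a 3:1 ratio of intervention to usual-care patients.

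The Statistical Methods paragraph under Effectiveness assessments defines the effect as the intervention group's change from baseline to 24 months minus the control group's change. It evaluates this by "mixed-effects models (PROC MIXED for continuous variables, PROC GLIMMIX for" "categorical variables), which included a random cluster effect (workplace). Group", with further adjustment for an unlisted set of baseline covariates and possible interactions. Neither sub-center nor matched set is named as a fixed effect, a random effect or a stratum. Since each sub-center has one control workplace, the two coincide. Appendices B and C both record a sub-center ID.

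**The concern.** A design that matches and assigns within strata is normally analysed with the strata in the model. There are two reasons to do so here.

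The first is bias. Each sub-center supplies one control workplace but one, two or three intervention workplaces. If the ratio varies, 3:1 sub-centers count for more in the intervention arm than in the control arm, and 1:1 sub-centers for less. A model without sub-center then compares two different regional mixes. Because no random allocation is described, nothing in the design rules out a link between the ratio and the region's own trend in blood pressure control.

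The second is precision. Variation between sub-centers that the matching removed from the comparison is still counted as error, so the reported standard error is larger than it need be.

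At stake are the size of the estimate and the width of its interval, for the primary outcome and for the secondary outcomes that use the same adjustment.

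**Working it through.** The protocol gives no figure on this point, so the check shows what its design implies under stated assumptions.

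**Inputs from the protocol.** 20 sub-centers; one control and one to three intervention workplaces in each; 3,000/75 = 40 intervention and 1,000/50 = 20 control workplaces; ICC 0.01; 20% loss, so 60 and 40 analysed patients per workplace; control rates of 50% and 20%.

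**Assumed.** The mix of ratios. With 7, 6 and 7 sub-centers at 1:1, 2:1 and 3:1 there are 7×1 + 6×2 + 7×3 = 40 intervention workplaces. A uniform 2:1 in all 20 also gives 40, so the protocol does not settle the mix.

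**Step 1: regional mix under 7/6/7.**
- 1:1 sub-centers: 7/40 = 17.5% of intervention and 7/20 = 35% of control workplaces.
- 2:1 sub-centers: 12/40 = 30% and 6/20 = 30%.
- 3:1 sub-centers: 21/40 = 52.5% and 7/20 = 35%.

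**Step 2: bias, counting workplaces equally.** Let k be the number of intervention workplaces in a sub-center and u its regional deviation in 24-month change. The bias is cov(k, u)/mean(k) = r × SD(u) × SD(k)/mean(k), where r is the correlation of k with u.
- If change is 5 points better in 3:1 and 5 points worse in 1:1 sub-centers, the bias is 5×(0.525 − 0.35) − 5×(0.175 − 0.35) = 1.75 points. This is perfect alignment.
- With r = 0.5 and mix 6/8/6, SD(k)/mean(k) = 0.387. The bias is 0.6, 1.0 and 1.9 points for SD(u) of 3, 5 and 10 points.
- With r = 0.5 and ten sub-centers each at 1:1 and 3:1, SD(k)/mean(k) = 0.5. The bias is 0.75, 1.25 and 2.5 points. Only with r = 1 and SD(u) = 10 does it reach 5.
- With r = 0, or one ratio throughout, the expected bias is 0.

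Simulation agreed, and with sub-center in the model the bias was at most 0.1 point.

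**Step 3: how extreme is the 5-point gradient?** Its variance is (14/20)×25 = 17.5 squared points, or 0.00175. Divided by 0.20×0.80 = 0.16 this is 0.011, which alone uses up the planned ICC of 0.01. A 10-point gradient has variance 0.007, an ICC of about 0.03 (against 0.25) to 0.04 (against 0.16).

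**Step 4: if the 3:1 patient ratio holds in each sub-center.** Each then contributes 40 analysed control and 120 analysed intervention patients, with m = 120/k per intervention workplace. Weighted by patients, the arms have the same regional mix and the bias is 0. Inverse-variance weights are proportional to k×m/(1 + 0.01(m − 1)): 54.8, 75.5 and 86.3 for k = 1, 2 and 3. The 1.75 points become 5×7×(86.3 − 54.8)/(7×54.8 + 6×75.5 + 7×86.3) = 0.77.

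**Step 5: precision under 7/6/7.** Without sub-center, the variance is 0.25×1.59/2,400 + 0.16×1.39/800 = 0.000444, so the SE is 2.11 points. With sub-center fixed and a share f of between-workplace variance regional:
- a = 0.25×[0.99/60 + 0.01(1 − f)] per intervention workplace;
- b = 0.16×[0.99/40 + 0.01(1 − f)] per control workplace;
- SE = [7/(a + b) + 6/(a/2 + b) + 7/(a/3 + b)]^(−1/2).

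The interval also reflects degrees of freedom: 60 − 2 = 58 (t = 2.002) against 39 (t = 2.023).

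| f | SE (points) | Change in SE | Change in CI width |
|---|---|---|---|
| 0% | 2.16 | +2% | +3% |
| 10% | 2.12 | +1% | +2% |
| 25% | 2.07 | −2% | −1% |
| 50% | 1.98 | −6% | −5% |
| 75% | 1.88 | −11% | −10% |

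Simulation confirms the direction. With ten sub-centers each at 1:1 and 3:1, regional SD 5 points and r = 0, the model SE without sub-center averaged 2.35 against a true spread of 1.99. With sub-center it averaged 1.99 against 2.01.

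**The case against.** The strongest reply is that the omission is not proven. The baseline covariates are not listed, sub-center could be among them, and a statistical analysis plan may say so. This stands in part: the protocol does not exclude sub-center. But sub-center is a design identifier and not a patient's baseline measurement, and the protocol is specific enough to name the procedures and the cluster effect, which is workplace alone.

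A reader might infer that any regional difference in blood pressure control biases the result. The documents do not support that. The effect is a difference in change, so stable differences in level largely cancel; what matters is a difference in 24-month change that is also associated with the ratio. A reader might also read the 3:1 patient ratio as applying within each sub-center, which the wording allows. Step 4 shows that this shrinks or removes the bias.

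A reader might further infer that the matching is wasted. It is not: balance on the matched characteristics remains in the design, and what is lost is precision, in the conservative direction. Nor is the gain as large as it first looks. Taking the regional share out of the ICC in the pooled formula suggests 4%, 8% and 13%, but this ignores the cost of estimating within strata of unequal ratio.

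Lastly, the planned effect of 25 points is about 12 standard errors (25/2.11), so a bias of 1 to 2 points would hardly alter the finding. That stands.

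**Conclusion.** The point holds in a limited form. The stated model does not name the stratum within which workplaces were matched and assigned. The resulting bias is roughly 1 to 2 points under adverse assumed gradients in change, less if the patient ratio is 3:1 in each sub-center, and zero in expectation if ratio and regional change are unrelated. Otherwise the cost is a conservative standard error, whose reduction by sub-center fixed effects ranges from about 11% to a small loss, depending on how much between-workplace variance is regional.

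The ratio mix, the regional spread and its correlation with the ratio are all assumptions; the protocol gives none of them. The primary conclusion is unlikely to change. The point is worth correcting because the bias can approach one standard error, because the same models serve the secondary outcomes, and because the remedy is nearly free.

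**What to change.** Add sub-center to every PROC MIXED and PROC GLIMMIX outcome model, with workplace as a random effect nested within it. A fixed effect with 20 levels is preferable, because a random intercept removes the bias less completely; keep the random intercept as a stated fallback if the fixed version does not converge. If sub-center was already meant to be among the baseline covariates, name it. It would also help to state whether the 3:1 patient ratio applies within each sub-center or overall.

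The cost is 19 of about 58 between-workplace degrees of freedom, and an interval about 2% to 3% wider if little or no variance lies between sub-centers. No new data are needed, since the sub-center ID is already collected.
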